#### Inclusion criteria

All pregnant women who planned for caesarean section and have consented for the study are eligible for inclusion in the study.

#### Exclusion criteria

All pregnant women with fever (temperature of 38°C and above), prolonged obstructed labor and premature rupture of membranes (rupture of membrane more than 12 hours will be excluded. Pregnant women presenting with features of chorioamnionitis (that is, foul smelling lochia, uterine tenderness associated with fever), allergic to the antibiotics used in the study or those who have used antibiotics in the 24 hours preceding the operation will also be excluded.

### Randomization

Intervention will start after allocating eligible candidates into two study arms: A and B.

Study arm A will be those who will receive a single intravenous single dose of gentamicin (3 mg/Kg) plus metronidazole 500 mg 30 to 60 minutes before operation. Study arm B will be those who will receive multiple doses of gentamicin (3 mg/Kg) plus metronidazole (500 mg) 30 to 60 minutes before operation and metronidazole 500 mg every 8 hours for 24 hours.

Simple randomization will be used to allocate study participants. About 490 opaque envelopes of the same size and color will be prepared for this study. A total of 245 envelopes will contain papers marked “study arm A” and the remaining envelopes will contain papers marked “study arm B”. Then all envelopes will be mixed thoroughly in a box before selection of an envelope is done.

Each study participant will select one sealed envelope and give it to the research assistant to open. Then, she will be administered antibiotic prophylaxis according to the study allocation group.

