## Abstract

**Background:**

Caesarean section is a commonly performed operation worldwide. It has been found to increase rates of maternal infectious morbidities more than five times when compared to vaginal delivery. Provision of intravenous prophylactic antibiotics 30 to 60 minutes prior to caesarean section has been found to reduce post-caesarean infection tremendously. Many centers recommend provision of a single dose of antibiotics, as repeated doses offer no benefit over a single dose.

At Bugando Medical Centre post caesarean infection is among the top five causes of admission at the post-natal ward. Unfortunately, there is no consistent protocol for the administration of antibiotic prophylaxis to patients who are designated for caesarean section. Common practice and generally the clinician’s preference are to provide repeated dosages of antibiotic prophylaxis after caesarean section to most of the patients. This study aims to determine the comparative efficacy of a single dose of gentamicin in combination with metronidazole versus multiple doses for prevention of post caesarean infection.

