**Methods/Design:**

The study is an interventional, open-label, two-armed, randomized, single-center study conducted at Bugando Medical Centre Mwanza, Tanzania. It is an ongoing trial for the period of seven months; 490 eligible candidates will be enrolled in the study. Study subjects will be randomly allocated into two study arms; “A” and “B”. Candidates in “A” will receive a single dose of gentamicin in combination with metronidazole 30 to 60 minutes prior to the operation and candidates in “B” will receive the same drugs prior to the operation and continue with gentamicin and metronidazole for 24 hours. The two groups will be followed up for a period of one month and assessed for signs and symptoms of surgical site infection.

Data will be extracted from a case record form and entered into Epi data3.1 software before being transferred to SPSS version 17.0 for analysis. The absolute difference in proportion of women who develop surgical site infection in the two study arms will be the effectiveness of one regime over the other.

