A number of well-designed studies have documented the efficacy of prophylactic antibiotics in reducing the rates of post-partum infection among patients who have undergone caesarian section [17-21]. Administration of antibiotic prophylaxis within an hour prior to skin incision is more effective in reducing post-caesarean infectious morbidity when compared to administration of the same drugs after cord clamping, and has no effect on neonatal infection [22-26]. Owens *et al.*, in a systematic review, reported that provision of antibiotic prophylaxis for caesarean section before skin incision compared with after umbilical cord clamping is associated with a 40% decrease in postpartum endometritis and a 30% decrease in wound infection [27].

Provision of a single dose of antibiotics preoperatively has been found to be as effective as multiple doses, in prevention of postpartum infection [28,29].

At Bugando Medical Centre (BMC), the rate of caesarian is estimated to be 20% [30]. All patients who deliver by caesarian section receive antibiotic prophylaxis. There is no consistent protocol for administration of antibiotic prophylaxis for patients designated for caesarean section The common practice is to provide repeated doses of prophylactic antibiotics for at least 24 hours after caesarian section and often on individual clinicians’ practice and preference. Gentamicin and metronidazole are among the antibiotics which are used as prophylaxis for infection during caesarean delivery.

This study aims to compare the efficacy of an intravenous single dose of gentamicin (3 mg/Kg) plus metronidazole 500 mg given 30 to 60 minutes before incision and multiple doses of gentamicin (3 mg/Kg) plus metronidazole (500 mg) 30 to 60 minutes before incision and every 8 hours for 24 hours postoperatively.

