### Study hypothesis

In this study, the hypothesis is: “there is no clinically significant difference between a single dose of gentamicin in combination with metronidazole and multiple doses over 24 hours for prevention of post caesarean infection".

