### Data collection

All data will be extracted from patients’ files and filled in a case record form designed for this study. Data to be collected will include the woman’s socio-demographic characteristics, obstetric history (past and present), and labor history if any (stage of labor, state of amniotic membrane-whether intact or ruptured) and others. Information on the HIV status of all women will also be collected. Patients’ information will be added during follow up.

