### Data analysis

Analysis will involve baseline and hypothesis testing. Baseline analysis will involve comparing of the baseline characteristics between the two study arms. Hypothesis testing will be done to determine if there is a significant difference in cumulative incidence of post-caesarian infection between women under single dose antibiotic regimen and those under the multiple-doses antibiotic regimen. The analysis will be done as per protocol. The absolute difference in the proportion of women who will develop surgical site infection in the two study arms will be the effectiveness of one regimen over the other. Results will be presented in cumulative incidence and as a relative ratio together with 95% confidence intervals and *P*-value. Sub-group analysis will be performed by logistic regression to determine the association between surgical site infection and other covariates, such as HIV status, duration of operation, stage of labor and so on. Covariates with *P*-value less than 0.05 will be considered significant. Efforts will be made to trace by calling those who will be lost to follow so as to determine their well-being, this information will be incorporated into the data collection form (Additional file 1).

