### Data dissemination and utilization

Apart from being part of a dissertation proposal for FL, effort will be made to publish the final results. Importantly, the findings will be used to create a protocol for use of antibiotics as operative prophylaxis.

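### Arm B is defined in conflicting ways: the Randomization section schedules repeat doses of metronidazole only, while the Abstract and Background repeat both drugs for 24 hours

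*Protocol article*

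**What the plan says.** The protocol article describes arm B's regimen in three places.

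- **Randomization** (main-text Methods): "multiple doses of gentamicin (3 mg/Kg) plus metronidazole (500 mg) 30 to 60 minutes before operation and metronidazole 500 mg every 8 hours", continuing for 24 hours. Arm A is given there as one pre-operative dose of gentamicin 3 mg/kg with metronidazole 500 mg.
- **Background**, closing statement of the aim: "multiple doses of gentamicin (3 mg/Kg) plus metronidazole (500 mg) 30 to 60 minutes before incision and every 8 hours for 24 hours postoperatively".
- **Abstract, Methods/Design**: after the pre-operative dose, arm B women "continue with gentamicin and metronidazole for 24 hours". No dose or interval is given for the continuation.

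The question is framed around the combination. The Abstract's Background paragraph describes it as the "comparative efficacy of a single dose of gentamicin in combination with metronidazole versus multiple doses for prevention of post caesarean infection", and the Study hypothesis section compares "a single dose of gentamicin in combination with metronidazole and multiple doses over 24 hours for prevention of post caesarean infection".

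**The concern.** The Randomization sentence disagrees with the other two descriptions and with itself. It promises more than one gentamicin dose, yet the only gentamicin it schedules is the pre-operative dose. It then names metronidazole a second time, with its own dose, as the drug to be repeated, so a reader could take the restriction as deliberate.

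The antibiotic schedule is the one thing that differs between the arms by design. If gentamicin were not repeated, the arms would differ only in metronidazole, which is not the comparison in the aim or the hypothesis. The Data dissemination and utilization section says that "the findings will be used to create a protocol for use of antibiotics as operative prophylaxis", so anyone applying the result must be able to read from the Methods which regimen was tested.

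There is a possible further consequence. The Data analysis section states: "The analysis will be done as per protocol". If that means a per-protocol population, arm B women cannot be classified as adherent until one schedule is fixed. The sentence may mean only that the protocol will be followed, so little weight is put on it here.

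**Working it through.** The plan gives no total dose for arm B, so there is no printed figure to reproduce. The check sets the texts side by side and counts the gentamicin that each one implies.

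**Step 1: the texts compared**

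| Section | Gentamicin after surgery | Metronidazole after surgery | Interval given |
|---|---|---|---|
| Abstract, Methods/Design | continued, 24 hours | continued, 24 hours | none |
| Background (aim) | repeated, 24 hours | repeated, 24 hours | 8-hourly |
| Randomization | announced as multiple, no schedule | repeated, 24 hours | 8-hourly, metronidazole only |

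**Step 2: inputs**

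- Gentamicin dose: 3 mg/kg (Background and Randomization).
- Arm A: one dose (Randomization).
- Number of post-operative doses, k: not stated. An 8-hourly course over 24 hours suggests k = 3. This is an assumption, shown over the range 2 to 4.

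**Step 3: total gentamicin**

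Under the Background wording, the arm B total is 3 mg/kg × (1 + k).

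| k (assumed) | Arm B | Arm A | Difference |
|---|---|---|---|
| 2 | 3 × 3 = 9 mg/kg | 3 mg/kg | 6 mg/kg |
| 3 | 3 × 4 = 12 mg/kg | 3 mg/kg | 9 mg/kg |
| 4 | 3 × 5 = 15 mg/kg | 3 mg/kg | 12 mg/kg |

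Under the schedule actually printed in the Randomization section, the arm B total is 3 × 1 = 3 mg/kg, and the difference from arm A is 3 − 3 = 0.

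**Step 4: what is not computed**

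No gentamicin total is derived from the Abstract, because it gives no interval. Metronidazole totals are not compared, because the Randomization section does not say when its 24 hours begin.

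**Step 5: can the article resolve the conflict?**

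The weight of the text favours repeating both drugs: the Abstract, the aim, the hypothesis and the Randomization section's own reference to multiple gentamicin doses all point that way. A gentamicin interval dropped from one sentence is the likelier explanation. No section says so, however, and none is given precedence over the others.

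**The case against.** The strongest reply is that the regimen can be recovered. The Background gives it in full for both drugs (dose, timing, interval and duration), the Abstract agrees, and no sentence says that arm B receives gentamicin only once. The harmful reading has to ignore part of the sentence it comes from. The zero difference depends on that less likely reading, and the 9 mg/kg figure depends on an assumed number of doses. The article also condenses a full protocol that is not shown and that may give staff a clear schedule, and nothing indicates that any woman was dosed wrongly. On this view the point is a wording slip.

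Much of this stands. Repeating both drugs is the probable intent, the dose figures are conditional, and the article proves nothing about how women were treated. It is also fair to say that the Abstract's Methods/Design paragraph describes the arms too, so the Randomization section is not the only place that does so.

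None of this removes the contradiction. The Abstract is one of the conflicting texts and cannot settle the conflict. Nor is this a detail left to a fuller document: the article states the regimen three times, and the main-text definition of the arms disagrees with the other two.

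**Conclusion.** The concern holds: the arm B definition is wrong as written and must be fixed. Depending on which section is followed, the planned gentamicin difference between the arms is 9 mg/kg (6 to 12 mg/kg for two to four post-operative doses, the number being an assumption) or zero. At zero, the trial would test repeat metronidazole only and would not address its hypothesis. The definition applies to the 245 women planned for arm B, half of the 490 to be enrolled.

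Confidence in the textual conflict is high. The metronidazole-only regimen is a risk created by the wording and not the likely intent, and there is no evidence that dosing was inconsistent in practice.

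**What to change.** Rewrite the arm B sentence under Randomization so that each drug has its own post-operative dose, interval, duration and number of doses.

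- **If both drugs are repeated** (the likelier case): state gentamicin 3 mg/kg and metronidazole 500 mg, each given 8-hourly over the 24 hours after surgery, in line with the Background. The Abstract and Background need no change. Cost: one sentence.
- **If only metronidazole is repeated:** remove the reference to multiple gentamicin doses under Randomization, correct the Abstract's Methods/Design paragraph and the Background, and restate the aim, the hypothesis and the eventual trial conclusion as concerning repeat metronidazole only. Cost: wording changes in five places (the Abstract's Background and Methods/Design paragraphs, the main Background, the Study hypothesis and Randomization).

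Use the corrected schedule for any per-protocol classification.

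The Trial status section says that recruitment started on 1 October 2011, so correcting the text does not by itself show what was given. Report the gentamicin and metronidazole doses that arm B women actually received. The source is already in use, since the Data collection section says: "All data will be extracted from patients’ files and filled in a case record form designed for this study". The extra cost is that extraction. Sample size, randomization and follow-up are unaffected.

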## Background

Postpartum infection remains among the top five causes of pregnancy-related maternal mortality and morbidity worldwide [1-3]. Women who undergo caesarean section have a 5- to 20-fold greater risk of postpartum infection than women having a vaginal delivery [4-7]. The incidence of post-cesarean infection varies widely worldwide from 2.5% to 20.5% [8-12].

Post-caesarean infections are polymicrobial, involving aerobes, anaerobes and ureaplasma. The main source of postpartum infection after caesarean section is the lower genital tract, particularly if the membranes are ruptured, but this still occurs with intact membranes following preterm birth. The most common isolated pathogens are anaerobes and gram-negative aerobes. Gram-negative aerobes include *Escherichia coli, Klebsiella* spp, *Enterobacter* spp. and *Proteus* spp*.* The anaerobes include *Bacteroides* spp*., Clostridium* spp.*,* and *Fusobacterium* spp*.*[8-10]*.* However, exogenous bacterial contamination by skin flora (such as *Staphylococcus aureus*) as a result of a break in sterile technique, may occur, especially following a difficult or complicated surgery [11]. Mawalla *et al.*, in a prospective cross-sectional study, reported that most common isolates in surgical site infection at Bugando Medical Centre are gram-negative bacteria. *Staphylococcus aureus* was found in only 28.6% of study patients; and 18.8% were MRSA (Methicillin resistant *Staphylococcus aureus*) [12].

Selection of antibiotics for prophylaxis follows the principle that the selected antibiotic regimen should have activity against the microbial agent commonly involved in surgical site contamination and actual infection. A combination of clindamycin and aminoglycosides has been recommended as the treatment of choice in post-caesarean infection, since it covers most of the pathogenic bacteria commonly involved. Alternatively, a combination of metronidazole with aminoglycosides has been found to be effective in some studies [8,10,13,14]. Apart from being a drug of choice in treating gram-negative bacteria, methicillin sensitive *Staphylococcus aureus* responds to gentamicin [14-16].

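### The treatment effect is set as an unadjusted difference in infection proportions; pre-specifying adjustment for two or three baseline factors already collected would gain a little precision and fix the adjusters in advance (low priority)

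*Protocol article*

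**What the plan says.** All places are in the protocol article.

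- **Randomization:** "Simple randomization will be used to allocate study participants". The method described is a box of 490 shuffled envelopes, of which "A total of 245 envelopes will contain papers marked" arm A and the rest arm B. The arm totals are therefore fixed, but no baseline factor is balanced by design.
- **Data analysis, effect measure:** the regimens are compared by a raw contrast: "The absolute difference in the proportion of women who will develop surgical site infection in the two study arms will be the effectiveness". No adjuster is named.
- **Data analysis, covariates:** "Sub-group analysis will be performed by logistic regression to determine the association between surgical site infection and other covariates". HIV status, duration of operation and stage of labor are given as examples. The section does not say whether study arm is in this model.
- **Data analysis, baseline:** "Baseline analysis will involve comparing of the baseline characteristics between the two study arms". Nothing is said about what follows if a difference is seen.
- **Data collection:** labor history includes "stage of labor, state of amniotic membrane-whether intact or ruptured", and HIV status is collected for all women.
- **Background:** the lower genital tract is named as the main source of infection after caesarean section, "particularly if the membranes are ruptured". No size of risk is given.

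**The concern.** The article points to ruptured membranes as relevant to infection, lists stage of labor and HIV status as covariates of interest, and collects all three. It then defines the treatment effect without them. Two things follow.

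First, variation in outcome that these factors explain stays in the standard error of the comparison. The trial has to rule out a 5-point difference with few events, so some precision is given up although the data are in hand.

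Second, a baseline comparison is planned with no stated consequence, next to a logistic model whose covariate list is open-ended. If an imbalance appears, the analyst could adjust or not, and for whichever factor, after seeing the data. One listed example, duration of operation, is not a baseline factor. The envelope is opened before prophylaxis, which itself precedes the operation by 30 to 60 minutes. Anyone who took that list as the adjustment set would be conditioning on a post-randomisation variable.

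**Working it through.** The article gives no figure for the gain from adjustment, so there is none to reproduce. The check asks how large the gain could be.

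**Inputs from the article (Sample size estimation, Randomization).** 245 randomised and 222 evaluable per arm; expected infection 8.1% (single dose) and 6.9% (multiple dose), mean 7.5%; difference D of 5 points; Z at 0.95, so one-sided 5%.

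**Assumed, not in the article.** Prevalence of a risk factor 10% to 50%; risk ratio 2 to 3. Two further illustrations have 50% prevalence and risks of 9% v 6% or 12% v 3%, each averaging 7.5%.

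**1. Expected events.** 444 × 0.075 = 33.3; 490 × 0.075 = 36.75.

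**2. Crude precision.** SE = sqrt[(0.081 × 0.919 + 0.069 × 0.931) / 222] = 0.0250. The 95% half-width is 1.96 × 0.0250 = 4.9 points.

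**3. Chance imbalance in one factor.** At 50% prevalence, 1.96 × sqrt(2 × 0.25 / 245) = 8.9 points. At 10% prevalence, 1.96 × sqrt(2 × 0.09 / 245) = 5.3 points.

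**4. Resulting shift in one realised estimate (edge of the 95% range).** 0.0885 × 0.09 = 0.80 points for 12% v 3%; 0.0885 × 0.03 = 0.27 points for 9% v 6%. Over prevalence 10% to 50% and risk ratio 2 to 3, the shift is 0.36 to 0.76 points.

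**5. Share of variance explained by one factor.** 0.25 × gap² / (0.075 × 0.925) = 2.9% for a gap of 0.09 and 0.3% for 0.03. Over the prevalence and risk-ratio grid it is 0.6% to 2.7%. Removing 2.9% narrows the half-width by 4.9 × (1 − sqrt(0.971)) = 0.07 points.

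**6. Three factors together, by simulation.** 8,000 trials per setting; 245 per arm with fixed totals; multiple-dose risk 6.9%; three binary factors with prevalence 30%, 50% and 10%; the same risk ratio (RR) for each. The crude difference is compared with a regression-adjusted risk difference with robust standard errors, and non-inferiority is judged at 5 points, one-sided 5%. Variance saved was calculated before rounding the SDs.

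| True difference (points) | RR each | SD crude | SD adjusted | Variance saved | Non-inferiority concluded, crude | adjusted |
|---|---|---|---|---|---|---|
| 0 | 2 | 2.29 | 2.28 | 1.5% | 71.4% | 71.7% |
| 0 | 3 | 2.27 | 2.20 | 5.8% | 70.9% | 73.3% |
| 1.2 | 2 | 2.36 | 2.33 | 2.0% | 49.6% | 49.7% |
| 1.2 | 3 | 2.39 | 2.32 | 5.2% | 49.0% | 50.1% |
| 5 | 2 | 2.64 | 2.62 | 1.6% | 5.3% | 5.5% |
| 5 | 3 | 2.63 | 2.57 | 4.2% | 5.4% | 5.2% |

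The mean crude estimate was within 0.03 points of the truth in every setting. Coverage of the 95% interval was 94.6% to 95.3% crude and 94.8% to 95.5% adjusted.

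The roughly 49% in the 1.2-point rows falls short of the planned 80% for a separate reason. With the usual variance terms, the stated inputs give 594 per group, not 222. That does not affect the comparison of crude with adjusted.

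**The case against.** The strongest objection is that nothing here is an error. An unadjusted risk difference is a standard primary analysis, and the simulation confirms that it is unbiased with correct coverage. This stands.

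A reader might infer more: that chance imbalance in known risk factors goes uncorrected into the result, or that the unstratified allocation is itself the defect. The documents do not support either. Imbalance can move one realised estimate, but the interval already includes that variation. Setting a 0.8-point shift against the expected 1.2 points also uses the wrong yardstick. The 1.2 is only about half of one standard error (1.2 / 2.5), and the conclusion rests on an interval with a 4.9-point half-width set against 5 points.

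Further points on that side, and what remains of them:

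- The prevalences and risk ratios are assumed. The exclusion of fever, features of chorioamnionitis, prolonged obstructed labor and rupture beyond 12 hours narrows the very risks concerned. This stands, so the lower end of the range is plausible.
- Data collection does not say when each item is recorded. Data come from patients' files and are added to during follow-up. This stands, and the fix must tie each adjuster to its value before allocation.
- The article does not rule out adjustment, and an analysis plan that is not shown may specify it. This stands in part. However, Data analysis does fix the effect measure and does give covariates a different role, so a reader of the article would take the primary result to be crude.
- Adjustment is not free. Strata may be sparse and an adjuster may be missing. This stands and limits the number of factors.

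One qualification runs the other way. Unbiasedness holds for all women randomised. Data analysis says the analysis is as per protocol; if that means a per-protocol set, balance is no longer assured by design. The wording is ambiguous, and baseline adjustment would be only a partial remedy, so the point does not rest on this.

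**Conclusion.** The point holds as a low-priority improvement in precision and pre-specification, not as a flaw in validity. Under the assumed prevalences and risk ratios, one factor accounts for about 0.3% to 3% of the variance of the difference. Three factors with a risk ratio of 3 each, a strong assumption, save 4% to 6%. The gain in the chance of concluding non-inferiority is 0.1 to 2.4 percentage points, and 0.1 to 1.1 at the article's own expected difference. The article gives no prevalence or effect size for any of these factors, so a larger benefit cannot be shown from it. The second benefit, fixing the adjusters before the baseline comparison is seen, does not depend on these assumptions.

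**What to change.** Leave the allocation as it is and change the Data analysis section:

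- Make the primary estimate a risk difference (single minus multiple dose) adjusted for two or three named factors, for example membrane status and stage of labor, each taken as it stood before the envelope was opened. Use Mantel-Haenszel stratification or a standardised risk difference from a logistic model that includes study arm, with its confidence interval.
- Report the crude difference as support.
- State that the baseline comparison is descriptive and will not be used to choose adjusters.
- Keep duration of operation out of the adjusters; it can stay in the separate model of association.
- Say how a missing adjuster value is handled.

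Recruitment began on 1 October 2011, so the change should be dated and made before outcomes are compared by arm.

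**Cost:** a few sentences and slightly more analysis work. No new data are needed. With about 33 to 37 events expected, more than two or three adjusters would not be supportable.
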